## Abstract

**Background:**

Physical inactivity is one of the leading modifiable causes of death and disease in Australia. National surveys indicate less than half of the Australian adult population are sufficiently active to obtain health benefits. The Internet is a potentially important medium for successfully communicating health messages to the general population and enabling individual behaviour change. Internet-based interventions have proven efficacy; however, intervention studies describing website usage objectively have reported a strong decline in usage, and high attrition rate, over the course of the interventions. Web 2.0 applications give users control over web content generated and present innovative possibilities to improve user engagement. There is, however, a need to assess the effectiveness of these applications in the general population. The Walk 2.0 project is a 3-arm randomised controlled trial investigating the effects of “next generation” web-based applications on engagement, retention, and subsequent physical activity behaviour change.

**Methods/design:**

504 individuals will be recruited from two sites in Australia, randomly allocated to one of two web-based interventions (Web 1.0 or Web 2.0) or a control group, and provided with a pedometer to monitor physical activity. The Web 1.0 intervention will provide participants with access to an existing physical activity website with limited interactivity. The Web 2.0 intervention will provide access to a website featuring Web 2.0 content, including social networking, blogs, and virtual walking groups. Control participants will receive a logbook to record their steps. All groups will receive similar educational material on setting goals and increasing physical activity. The primary outcomes are objectively measured physical activity and website engagement and retention. Other outcomes measured include quality of life, psychosocial correlates, and anthropometric measurements. Outcomes will be measured at baseline, 3, 12 and 18 months.

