The 10,000 Steps program is one example of a novel PA promotion project that was initially established as a whole-of-community study known as the 10,000 Steps Rockhampton project [25,26]. Since the completion of the original project, the program has continued to be disseminated at the individual and community levels [5]. A key element of the dissemination of the program has been the use of the Internet to promote and support PA. The 10,000 Steps website has been used to disseminate PA information to health professionals and to provide engagement of registered members through the use of an online step log. The website is generally used in conjunction with a pedometer, one of the novel elements of the original program, and web-based ‘i-challenges’ and ‘virtual journeys’. The 10,000 Steps website has demonstrated that the self-monitoring characteristic of the site (use of i-challenges) is a strong factor in retaining users [27,28]. This is consistent with research demonstrating that pedometers are useful as self-monitoring and motivational tools, and also a significant factor in increasing PA in a broad range of population groups including people with type 2 diabetes [29], insufficiently active women [30], and people engaged in a web-based worksite PA program [31]. Pedometer step logs, in conjunction with activities such as challenges and ‘virtual journeys’, are basic examples of the type of interactivity that can be created using Web 1.0 technology, which may further enhance the capacity of websites to retain users and produce more sustainable changes in PA.

In this study we plan to compare the use of Web 1.0 applications, as applied in the Australian 10,000 Steps website, with Web 2.0 applications. Our aim is to investigate the effects of “next generation” web-based applications (e.g. social networking), to establish whether Web 2.0 technology can outperform Web 1.0 technology in terms of website engagement, retention and subsequent PA behaviour change.

Primary Hypothesis:

H1: Participants in the Web 2.0 condition will display higher levels of physical activity at 3 months, and at 12 and 18 months post intervention, compared with the Web 1.0 or control condition.

Secondary Hypothesis:

H2: There will be significantly greater website engagement and participant retention on the website in the Web 2.0 arm of the study than in the conventional (Web 1.0) condition at 3 months, and at 12 and 18 months post intervention.

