### Study procedure

Participant eligibility will be screened through a self-administered survey that is delivered with a personalised invitation letter (AEC-recruited participants) and a reply-paid envelope. Online access to the screening survey will also be available for all potential participants. As indicated above, additional screening concerning PA and health status may be needed for some people. All those deemed eligible will then be contacted by telephone and invited to attend an induction session to provide informed consent and be fitted with an ActiGraph activity monitor to measure PA, which they are required to wear for 7 days. Participants will be asked to complete a log of wear time, showing time that the monitor was put on and taken off each day and the time and reason that the monitor was taken off during the day. When participants return the ActiGraph (at least 8 days later) they will participate in the baseline measurement session. All measurements sessions (baseline, 3, 12 and 18 months) will incorporate anthropometic measures and a self report questionnaire (Table 1) and will be conducted at a University campus. ActiGraph monitors will be posted to participants by registered post for 3, 12 and 18 month follow ups a week before they attend their measurement session at the university. Participants will be randomly allocated to an intervention condition and all participants will receive a pedometer (Yamax Digiwalker SW200, Yamasa Tokei Keiki co., Japan) after satisfactorily completing the requirements of the baseline measurement (valid Actigraph data, completed anthropometric assessments, completed baseline survey). Participants’ progress and use of the website will not be monitored between follow-up measurement points.

**Table 1 T1:** Summary of measures to be collected

**Primary outcome measures**	**Data collection instrument**	**Collection points (months)**
Physical activity levels	7 day ActiGraph physical activity monitoring	0, 3, 12 and 18
	Active Australia Survey [35]	0, 3, 12 and 18

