#### Other measures

Website usage, engagement, and retention for the Web 1.0 and Web 2.0 intervention groups will be measured using a commonly available web traffic analysis platform (Google analytics) and monitoring of user-generated content. Features monitored will include:

• Number of logins

• Frequency of step log use (and steps logged)

• Use of site stream (status updates, and comments on ‘friends’ stream)

• Page visits

• Goals set

• Time on website

• Number of friends (Web 2.0 only)

• Number of blog posts

In the Control group, logbooks will also be collected to enable comparison in use of common features (e.g., step log, goal setting) between interventions.

Quality of life will be assessed with the RAND 36 item Short Form Health Survey (SF-36) which evaluates 8 health concepts including limitations in physical activities and usual role activities because of health problems, bodily pain, general mental health, and vitality (energy and fatigue). The SF-36 has been validated on Australian populations [51], has demonstrated suitability for use in the general population [52,53], and is associated with the stage of motivational readiness to changes in physical activity [54,55].

Participants’ confidence in their ability to execute tasks and trouble shoot problems with the Internet will be measured using the Internet Self-Efficacy Scale (ISES). The effect of Internet self-efficacy is poorly understood in terms of Internet-delivered PA programs. The ISES uses 8 items assessed on a 7-point likert scale to assess a user’s understanding of Internet hardware and software, confidence in gathering information using the Internet and learning skills to use Internet programs, and ability to troubleshoot and resolve Internet problems. The ISES has shown good reliability and internal consistency [43].

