### Statistical power and sample size

Sample size for the RCT is based on the primary outcome measure, minutes of MVPA, as measured by the ActiGraph accelerometer. A review of web-based PA interventions suggests that studies which do not include aspects of Web 2.0 had a small effect on change in PA status of participants and had a dropout rate of approximately 40% [15]. Given the enhanced effects of the Web 2.0 intervention expected on the PA status of participants, the current study will be powered to detect a small to moderate change in minutes of MVPA. Therefore, to achieve 80% power to detect a small to moderate difference in PA between groups (control/Web 1.0/Web 2.0) at any given time point, approximately 120 participants per group will be required using an alpha level of 0.05. The number of participants per group has been inflated by 40% (n=168/group) to account for participant drop out while retaining adequate power to achieve study aims at 18 months.

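### ActiGraph activity is primary throughout, but the protocol article contradicts itself on whether website engagement and self-reported activity are primary too

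*Protocol article*

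**What the plan says.** Five places in the protocol article bear on which outcomes are primary.

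- **Abstract, Methods/design:** "The primary outcomes are objectively measured physical activity and website engagement and retention". This is plural, includes website engagement, and restricts activity to objective measurement.
- **Background, hypotheses:** the primary hypothesis is about activity only and names no instrument: "H1: Participants in the Web 2.0 condition will display higher levels of physical activity at 3 months". The secondary hypothesis reads "There will be significantly greater website engagement and participant retention on the website in the Web 2.0 arm of the study", with the Web 1.0 arm as comparator.
- **Study procedure, Table 1:** under "Primary outcome measures" there is one construct, physical activity, with two instruments: "7 day ActiGraph physical activity monitoring" and the Active Australia Survey, both at 0, 3, 12 and 18 months. Website engagement and retention appear nowhere in the table.
- **Outcome measurements:** the Physical activity subsection describes the survey as subjective and the ActiGraph as objective, and does not rank them. Under Other measures: "Website usage, engagement, and retention for the Web 1.0 and Web 2.0 intervention groups will be measured". Eight usage features follow, none singled out.
- **Statistical power and sample size:** here the wording is singular and allows one outcome only: "Sample size for the RCT is based on the primary outcome measure, minutes of MVPA, as measured by the ActiGraph accelerometer".

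The Statistical analysis section sets one alpha of 0.05 and does not divide it among outcomes.

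**The concern.** Two outcomes have conflicting status. Website engagement and retention are primary in one place, secondary in another, under Other measures in a third, and missing from the table of measures. Self-reported activity is primary in Table 1, but it is excluded by the Abstract's restriction to objective measurement and by the single outcome in the sample-size section.

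What is at stake is which result may be called primary when the trial reports. Accelerometer and questionnaire activity can disagree, and a website can hold its users without raising their activity. If ActiGraph MVPA is null and one of the other two is favourable, an author could cite part of this article in support of a positive primary finding, and a reader could cite another part against it. Participants presumably know whether they were given a website or a logbook, so the self-report route is also the one more open to reporting bias. That last point is an inference from the interventions; the article does not discuss blinding.

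**Working it through.** **1. Status of each outcome, side by side**

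| Place | ActiGraph activity | Active Australia Survey | Website engagement/retention |
|---|---|---|---|
| Abstract | primary | excluded (objective only) | primary |
| H1 / H2 | H1, instrument not named | H1, instrument not named | secondary (H2) |
| Table 1 | primary | primary | not listed |
| Other measures | – | – | listed here |
| Sample size | the single primary outcome (minutes of MVPA) | not named | not named |

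The first column is consistent. The second and third are not. Setting the Abstract aside as loose wording clears the third column's conflict over primary status, but Table 1 and the sample-size section still disagree about the survey.

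**2. What the stated alpha and power attach to**

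Inputs from the sample-size section: 80% power, alpha 0.05, about 120 per group. No numerical effect or SD is given, so the size cannot be reproduced forwards. Solving backwards for two means (two-sided test assumed):

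d = (1.960 + 0.842) × √(2/120) = 0.362

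This fits the article's description of a small to moderate difference. The inflation is 120 × 1.4 = 168 per group, and 168 × 3 = 504, as stated. All of this concerns ActiGraph MVPA. Neither the survey nor engagement has a power basis.

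**3. Illustration of the error rate**

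Take one comparison at one time point, one two-sided test at 0.05 per outcome, and suppose any significant outcome counts as success. For k independent outcomes the false-positive chance is 1 − 0.95^k:

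- k = 1: 5.0%
- k = 2: 1 − 0.9025 = 9.75%
- k = 3: 1 − 0.8574 = 14.3%

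With correlated outcomes (simulation of 400,000 normal draws; the correlations are assumptions, since the article gives none):

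| Correlation | Two outcomes | Three outcomes |
|---|---|---|
| 0.3 | 9.4% | 13.6% |
| 0.5 | 9.1% | 12.5% |
| 0.7 | 8.3% | 10.9% |

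The case of two covers either the Abstract's pair or Table 1's pair. The case of three adds both extras and applies only to Web 2.0 versus Web 1.0. Engagement and retention count as a single test here, although eight features are listed. Errors in both directions are counted. Counting only those favouring Web 2.0, the independent-case figures are 2.5%, 1 − 0.975² = 4.9% and 1 − 0.975³ = 7.3%.

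**4. Power if several primaries were kept with an equal alpha split**

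Power = Φ(d√(n/2) − z), with n = 120 and d = 0.362, so d√(n/2) = 2.802:

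- alpha 0.05: Φ(2.802 − 1.960) = 80%
- alpha 0.025 (two): Φ(2.802 − 2.241) = 71%
- alpha 0.0167 (three): Φ(2.802 − 2.394) = 66%

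**The case against.** The best defence is that ActiGraph activity is primary wherever an instrument is named, H1 is about activity alone, and the sample size rests on that one measure. On engagement, the Abstract is the outlier. Table 1 lists one primary construct with two instruments, which need not mean two co-primary endpoints. The survey is cited as reliable, valid and able to detect intervention-related change. An analysis plan not shown may set the order.

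Much of this stands, and it rules out some stronger readings.

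- A reader might infer that the trial has no defined primary outcome, so that its 0.05 and 80% belong to no claim. The sample-size section attaches both to ActiGraph minutes of MVPA.
- A reader might count two comparators, three follow-up times and two instruments as 12 tests and quote a family-wise error of 38%, against 22% for six tests. Those figures need assumed correlations (0.5 between times, 0.3 between instruments) and a rule that any one test suffices, which the article does not state. The 22% comes from comparators and time points, a separate issue that settling the outcomes would leave untouched. Neither figure measures the engagement contradiction.
- A reader might think engagement could yield a positive result against control. H2 and the website measures concern the two web arms. Logbooks allow control comparisons only on shared features such as step logging.

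The defence does not remove the conflict. The survey sits under a primary heading while another section allows one primary outcome, and engagement is called primary in the Abstract. An analysis plan could agree with only one of these published statements.

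**Conclusion.** The point holds as a contradiction in labelling, confined to what is primary besides ActiGraph activity. It is wrong as written, rather than detail left to another document, and it changes which result may be reported as primary.

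The contradiction itself rests on no assumption. The error-rate illustration does: it supposes separate tests at 0.05 and success on any one. On that footing, 5% becomes about 9–10% with two outcomes (correlation 0 to 0.5) or 11–14% with three (0 to 0.7), per comparison and time point. The sample-size basis for ActiGraph MVPA is not affected by this point.

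**What to change.** Name ActiGraph minutes of MVPA as the sole primary outcome in the Abstract, H1, Table 1 and the Statistical analysis section, as the sample-size section already assumes. Label the Active Australia Survey and website engagement and retention as secondary, and add engagement and retention to Table 1.

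This costs wording only; no sample-size change follows. The sponsor gives up the option of calling a self-report or engagement result primary.

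If the sponsor prefers several primaries, any one of which would suffice, they should be declared as such, with a stated alpha split and restated power. With an equal split at 120 per group and the back-calculated effect, power for ActiGraph MVPA would be about 71% with two or 66% with three. The survey and engagement would each need a power basis of their own, and engagement a single defined measure.

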**Discussion:**

The findings of this study will provide increased understanding of the benefit of new web-based technologies and applications in engaging and retaining participants on web-based intervention sites, with the aim of improved health behaviour change outcomes.

**Trial registration:**

Australian New Zealand Clinical Trials Registry, ACTRN12611000157976

## Background

Physical inactivity remains one of the leading modifiable causes of death and disease in Australia [1]. Regular physical activity (PA) decreases the risk of developing cardiovascular disease, diabetes, some cancers, obesity, osteoporosis, and other chronic conditions [2], but national Australian surveys indicate that almost 60% of Australians aged 15 years and over do not undertake sufficient PA to obtain health benefits [3]. It has been estimated that physical inactivity contributes to more than 8,000 deaths in Australia each year, and that for every 1% increase in the Australian population becoming sufficiently physically active some $7.2 million in health care costs could be saved [4]. Novel approaches for increasing PA with the potential to reach broad populations at an acceptable cost are needed.

Interventions delivered via the Internet have emerged as a novel and popular health promotion strategy, with the potential for wide population reach. The Internet is potentially an important medium in communicating messages associated with raising the profile of PA to the general population [5,6]. Over the past decade, there has been unprecedented growth in the use of the Internet world-wide [7,8]. For example, in Australia (the focus of this trial) in 2010–2011 79% of homes had Internet access and there were over 6.2 million households with broadband Internet access (73% of all homes), showing a five-fold increase over the past ten years in Australia [9] and six-fold increase worldwide [7]. Internet users are also becoming more representative of the overall population, as more women, elderly, and people from low socio-economic background are going online [10]. The exponential growth of the Internet has been paralleled by research into the uses of the Internet for social marketing and health promotion [11]. Recent reviews of the effectiveness of Internet-based PA interventions have also demonstrated the short-term efficacy of this medium for individual behavioural change, but also the need to increase user interaction and retention to websites to increase long-term behavioural outcomes [12-15].

To obtain the social marketing, health promotion, and behavioural change benefits associated with Internet-delivered PA interventions, the engagement and retention of participants in larger and more representative study samples must be addressed [15]. Intervention studies that have provided objective data on website usage have reported a strong decline in usage, and high attrition rate over the course of the intervention [15]. A low level of website interactivity has been suggested as an explanation for the modest retention and engagement rates within these health promotion trials [16]. There is consensus in the literature that website-delivered behavioural change interventions with a high degree of interactivity are more effective in producing behaviour change compared to those with a low degree of interactivity [17,18].

Web 2.0 represents the newest generation of Internet-based, highly interactive applications, which are aimed at giving users control of how information is generated, created, and shared. Web 2.0 applications, including blogs, wikis, podcasts, mash-ups, and social networking sites, are widely embraced and their popularity continues to grow. For example, in Australia, there are currently over 11 million people who use the social networking website Facebook, with 75% of users going to the site at least once a day [19]. Hence, there are a growing number of speculative theses on the potential of Web 2.0 applications in the fields of health and medicine [20-24]. There is a clear need for larger population studies to examine this next generation of web-based applications (Web 2.0) and to study their effectiveness relative to conventional web-based approaches (Web 1.0), particularly with regard to participant engagement, retention, and PA behaviour change.

The 10,000 Steps program is one example of a novel PA promotion project that was initially established as a whole-of-community study known as the 10,000 Steps Rockhampton project [25,26]. Since the completion of the original project, the program has continued to be disseminated at the individual and community levels [5]. A key element of the dissemination of the program has been the use of the Internet to promote and support PA. The 10,000 Steps website has been used to disseminate PA information to health professionals and to provide engagement of registered members through the use of an online step log. The website is generally used in conjunction with a pedometer, one of the novel elements of the original program, and web-based ‘i-challenges’ and ‘virtual journeys’. The 10,000 Steps website has demonstrated that the self-monitoring characteristic of the site (use of i-challenges) is a strong factor in retaining users [27,28]. This is consistent with research demonstrating that pedometers are useful as self-monitoring and motivational tools, and also a significant factor in increasing PA in a broad range of population groups including people with type 2 diabetes [29], insufficiently active women [30], and people engaged in a web-based worksite PA program [31]. Pedometer step logs, in conjunction with activities such as challenges and ‘virtual journeys’, are basic examples of the type of interactivity that can be created using Web 1.0 technology, which may further enhance the capacity of websites to retain users and produce more sustainable changes in PA.

In this study we plan to compare the use of Web 1.0 applications, as applied in the Australian 10,000 Steps website, with Web 2.0 applications. Our aim is to investigate the effects of “next generation” web-based applications (e.g. social networking), to establish whether Web 2.0 technology can outperform Web 1.0 technology in terms of website engagement, retention and subsequent PA behaviour change.

Primary Hypothesis:

H1: Participants in the Web 2.0 condition will display higher levels of physical activity at 3 months, and at 12 and 18 months post intervention, compared with the Web 1.0 or control condition.

Secondary Hypothesis:

H2: There will be significantly greater website engagement and participant retention on the website in the Web 2.0 arm of the study than in the conventional (Web 1.0) condition at 3 months, and at 12 and 18 months post intervention.

